## Abstract

**Background:**

Despite global goals to improve maternal, newborn, and child health outcomes, mortality and morbidity continue to be a concern, particularly during the postnatal period in low- and middle-income countries. While mothers have the responsibility of providing ongoing care for newborns at home, they often receive insufficient newborn care education in Tanzania. Mobile health via text messaging is an ever-growing approach that may address this gap and provide timely education.

**Objective:**

We aim to evaluate a text message intervention called Essential Coaching for Every Mother Tanzania (ECEM-TZ) to improve maternal access to essential newborn care education during the immediate 6-week postnatal period.

**Methods:**

ECEM-TZ consists of standardized text messages from birth to 6 weeks post partum that provide evidence-based information on caring for their newborn and recognizing danger signs. Messages were developed and then reviewed by Tanzanian mothers and nurse midwives before implementation. A hybrid type 1 randomized controlled trial will compare ECEM-TZ to standard care among mothers (n=124) recruited from 2 hospitals in Dar es Salaam. The effectiveness outcomes include newborn care knowledge, maternal self-efficacy, breastfeeding self-efficacy, maternal mental health, attendance at the 6-week postnatal checkup, and newborn morbidity and mortality. The implementation outcomes include the reach and quality of implementation of the ECEM-TZ intervention.

**Results:**

Recruitment for this study occurred between June 13, 2024, and July 22, 2024. A total of 143 participants were recruited, 71 in the control and 72 in the intervention. The 6-week follow-up data collection began on July 30, 2024, and was completed on September 21, 2024.

**Conclusions:**

This study will generate evidence about the effectiveness of implementing text messaging during the early postnatal period and the feasibility of doing so in 2 hospitals in Dar es Salaam. The intervention has been designed in collaboration with mothers and nurse midwives in Tanzania.

**Trial Registration:**

ClinicalTrials.gov NCT05362305; https://clinicaltrials.gov/study/NCT05362305

**International Registered Report Identifier (IRRID):**

DERR1-10.2196/63454

## Introduction

### Background

The postnatal period during the first 6 weeks of life is a critical time point for newborns and mothers in Tanzania, which has a neonatal mortality ratio of 20 per 1000 live births [1] and a maternal mortality ratio of 104 per 100,000 live births [2]. Neonatal and maternal mortality is highest in the first week post partum [3,4]. Despite the high number of deaths that occur postnatally, most mothers and their newborns receive insufficient care during this period, especially in low- and middle-income countries (LMICs) [5]. There is a significant need to develop and evaluate innovative approaches to reach mothers during this period to ensure they are knowledgeable and confident in caring for their newborns at home.

While most Tanzanian women (90%) have at least 1 antenatal care contact, only half (51%) of the women and 54% of the infants receive postnatal care within 2 days after giving birth [2]. Further, health facilities are often unable to provide individualized education based on maternal needs due to staff shortages and resource constraints [6-8]. Across Tanzania, mothers receive little education about how to care for their newborns before hospital discharge due to significant health system challenges [6,8,9].

One innovative strategy that can be used to provide postnatal education directly to parents is mobile health (mHealth) [10]. The goal of mHealth interventions delivered postnatally is not to replace the need for in-person follow-up but to complement existing care and fill knowledge gaps by providing timely, standardized, relevant, and evidence-based information on newborns’ care at home. The use of mobile phones to reach mothers is supported by the World Health Organization recommendations, which state that traditional postnatal contact can be enhanced through mobile phone–based contact between mothers and the health system [11].

Due to the severe shortage of health care providers and the low rate of in-person postnatal contacts in Tanzania [12], Essential Coaching for Every Mother Tanzania (ECEM-TZ) is poised to bridge this gap without adding a significant burden to the health system. The goal of the ECEM-TZ intervention is to improve maternal access to knowledge during the immediate 6-week postnatal period, and to increase maternal self-efficacy and improve mental health outcomes.

### Effectiveness Objectives

The objective is to compare mothers who receive ECEM-TZ to mothers who receive standard care on newborn care knowledge, maternal parenting self-efficacy, breastfeeding self-efficacy, postpartum depression symptoms, anxiety symptoms, postnatal care attendance, newborn morbidity, and newborn mortality at 6 weeks post partum.

### Effectiveness Hypotheses

Mothers who receive ECEM-TZ will have higher levels of newborn care knowledge, maternal parenting self-efficacy, breastfeeding self-efficacy, and postnatal care attendance and lower rates of postpartum depression symptoms, anxiety symptoms, and newborn morbidity and mortality at 6 weeks post partum in comparison to those who received standard postpartum care.

### Implementation Objectives

The objective is to explore the implementation extent and quality of ECEM-TZ*.* Using process evaluation guidelines [13,14], the specific questions for ECEM-TZ are as follows:

*Recruitment effectiveness*: was this study able to recruit the desired number of participants in the time frame? Is there a difference in recruitment based on hospital level? What is the recruitment rate (ie, approached vs randomized)?*Implementation extent*: what was delivered, including the quality (fidelity), dose delivered (completeness), dose received (exposure), satisfaction, reach (participation rate), and recruitment?*Implementation quality*: what were the barriers and facilitators in implementing behavior change based on ECEM-TZ content? What is the level of satisfaction of ECEM-TZ?

## Methods

### Study Design

This is a 2-arm, parallel-group, hybrid type 1 randomized controlled trial (RCT). Participants will be randomized to receive a 6-week postpartum text message program called ECEM-TZ or standard care (no messages) with a 1:1 allocation*.*

A hybrid type 1 RCT study focuses on evaluating clinical outcomes while also seeking to understand the context for future implementation through a process evaluation [15,16]. For this protocol, a hybrid type 1 RCT study was selected as ECEM-TZ is a new digital health solution and thus, exploring whether the intervention improves clinical outcomes is the key focus. However, it is also important to explore the implementation factors related to extent and quality as well as recruitment effectiveness to ensure that the intervention effectiveness outcomes are not put at risk or misinterpreted if the digital health solution is not able to be implemented as intended.

### Intervention

#### ECEM-TZ Development (Pre-RCT Phase)

To create a standardized, evidence-based approach to the content, the initial messages were developed using the World Health Organization guidelines for postnatal care [11]. There were 54 unique messages initially developed: 6 related to the research study, 6 on postnatal care, 7 on feeding, 3 on handwashing, 3 on cord care, and 4 on thermal care. For messages related to danger signs, 5 each were on fever and breathing with 3 each on feeding, no movement, jaundice, cord infection, and convulsions. ECEM-TZ messages were designed to be tailored to each participant in that all mothers will receive the same content but may include the name of the mother or child. All text messages were developed in English and then translated into Kiswahili using standardized forward-backward translation processes [17] before testing.

All messages mapped onto the social cognitive theory of behavior change [18,19] and included four types: (1) educational, (2) reminders, (3) social support, and (4) interactivity (two-way), all to reinforce positive behaviors associated with newborn care. Educational messages provided one-way information about essential newborn care to encourage action, such as exclusive breastfeeding and hygiene cord care. Reminder messages consisted of one-way messages about upcoming postnatal contacts and returning to a clinic if they recognize a danger sign. Social support messages included messages from other fictional mothers encouraging them to provide evidence-based care. Finally, interactivity (two-way) messages included options for mothers to respond to inquiries, such as checking into whether they visited a postnatal clinic within the past seven days.

To ensure that the content of ECEM-TZ was appropriate and acceptable, the messages underwent two rounds of iterative testing with Tanzanian mothers and nurse midwives. Mothers were eligible for inclusion if they met the following criteria: (1) had recently given birth within the hospital; (2) were aged older than 18 years; and (3) spoke and read English or Kiswahili. Mothers were excluded if (1) their newborn died or was expected to die before leaving the hospital or (2) they were experiencing major postnatal complications expected to impact their ability to provide informed consent (eg, major postpartum hemorrhage or seizures). Nurse midwives were eligible to participate in this study if they (1) worked in a hospital on a labor or postnatal ward for at least three months to ensure that they had experience providing care to this population, (2) were currently involved in providing maternal and newborn care either on the labor ward or postnatal unit, and (3) could speak and read English or Kiswahili. Nurse midwives were excluded if they were not on duty during the data collection period.

On recruitment and before starting the interview, oral and written consent was obtained for this study’s purpose, as well as consent for the use of a voice recorder by all participants. Interviews were conducted by a research assistant at the hospital in a comfortable location as suggested by the participant. Participants were shown messages based on the topic area and asked: “What do you think this phrase is saying? Does anything come to mind when you read this? Are there any words that you did not understand? Was anything in this unacceptable or offensive? Are there any words you would suggest that could be used instead? If so, which one conforms best to your usual language?” Mothers were also asked to review and complete the Karitane Parent Confidence Scale [20], which was translated into Kiswahili. Interviews were transcribed verbatim and translated into English by a Tanzanian research assistant to facilitate analysis. A summary of concerns for both the Karitane Parent Confidence Scale and ECEM-TZ was created during each round of testing. Changes were made to the text messages based on participant feedback and any revisions were retranslated in Kiswahili. Final messages were translated back into English for backward translation to ensure the message remained intact and evidence-based [17].

In total, 10 mothers and 7 nurse midwives participated in the validation. In round 1, three mothers and 3 nurse midwives provided feedback, and in round 2, seven mothers and 4 nurse midwives provided feedback. Mothers were on average aged 27.4 (SD 5.1) years and had 1 (SD 1.4, range 0-4) other child. Nurse midwives were on average aged 37.4 (SD 8.9) years and had 10.8 (SD 6.9, range 1-19) years of clinical experience.

#### Final Intervention

ECEM-TZ is a one-way text message program sent from the third day after birth until 6 weeks postnatally. Messages are sent once per day in the morning. After 2 rounds of testing, the ECEM-TZ was finalized with a total of 44 messages that covered the following topics: 4 related to the research study, 7 on feeding, 6 on postnatal care follow-up, 4 on normal development, 3 each on thermal care and maternal care, and 2 each on cord care and handwashing. For messages related to danger signs, 3 each were on fever, no movement, or convulsions; 2 each were on poor feeding, jaundice, and breathing; and 1 was on cord infection. Given participant feedback during the pretesting, social support and two-way messages were removed due to reported poor participant acceptance and perceived clarity. Thus, only educational and reminder messages were included. No changes in care or education will be implemented, with mothers in the intervention group receiving standard in-hospital education as provided to all women delivering at that hospital before discharge from the postpartum unit. Mothers will be able to message “acha” (stop in Kiswahili) to withdraw from this study at any time and will stop receiving messages.

### Control Group

No changes in care or education will be implemented, with mothers in the control group receiving standard in-person education as provided to all women delivering at that hospital before discharge from the postpartum unit. Mothers will not receive any text messages from the program.

### Procedure (RCT)

Mothers will be recruited by a research assistant after giving birth at a health care facility and before discharge. Mothers will be approached and informed about this study. If interested, mothers will be screened against eligibility criteria. Eligible and consenting mothers will complete a baseline questionnaire (T1) and are then randomized into a study group. All participants will be followed up at six weeks postnatally (T2) via telephone.

### Randomization, Allocation, and Blinding

Using a 1:1 allocation, participants will be randomized into either the intervention or control group using a computer-generated stratified block randomization with blocks varying between 4 to 8 via REDCap (Research Electronic Data Capture; Vanderbilt University). Stratification based on the site of recruitment will be implemented. Due to the nature of ECEM-TZ, blinding will not be possible for mothers (ie, mothers will know if they receive text messages or not). To minimize bias at the participant level, all mothers will receive the same in-hospital care. Due to the nature of the intervention, mothers in the control group will not be exposed to the intervention text messages. Hospital staff (nurse midwives, physicians, and other health care providers) will be blind to participant group allocation to ensure both groups receive the standard discharge education. The researchers will be aware of participant allocation but will not be involved in data collection from participants or the randomization process. The research assistants will be blinded to allocation at baseline (T1) but not at T2.

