### Ethical Considerations

Ethics approval has been received from Dalhousie University (REB#2018-4538), Muhimbili University of Health and Allied Science (REB#MUHAS-REC-7-2019-010), and National Medical Institute of Research (REB#NIMR/HQ/R.8c/Vol.I/2457). All participants will be provided with written and verbal information and will complete a written consent form before enrollment in the study. To maintain confidentiality, all study data will be identified using a study number unique to each participant on all questionnaires and surveys. All data will be entered into REDCap by a research assistant in Tanzania with the first author having access to the data. REDCap is a secure web application for building and managing online surveys and databases [21]. All participants will receive the equivalent of honorarium (TZS 10,000; approximately US $4) in phone vouchers to their airtime provider of choice.

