### Effectiveness Outcomes

To measure the effectiveness of ECEM-TZ, the following will be assessed:

Newborn care knowledge: Knowledge will be assessed using a modified questionnaire developed by McConnell and colleagues [22] assessing newborn care knowledge. The questions determine whether mothers can identify danger signs, handwashing practices, cord care, newborn thermal care, and breastfeeding. A total sum of the number of items mothers can identify will be created. Additionally, binary variables will be created to determine whether mothers can identify three or more newborn danger signs, two or more best practice hand washing, two or more cord care practices, three or more thermal care practices, and two or more breastfeeding practices. Based on these variables, a summative score will be created ranging from 0 to 5, with a higher score representing increased newborn care knowledge.Maternal self-efficacy: Parenting self-efficacy will be measured using the Karitane Parenting Confidence Scale [20]. This 15-item scale was developed to assess the perceived self-efficacy of mothers of newborns from birth to aged twelve months and has acceptable internal consistency (Cronbach α=0.81) and test-retest reliability (*r*=0.88) [20]. A cutoff score of 39 or less (out of a possible 45) was determined to be a clinically low perceived parenting self-efficacy [20]. The Kiswahili version was piloted as part of the development phase.Breastfeeding self-efficacy: Breastfeeding self-efficacy will be measured using the Breastfeeding Self-Efficacy Scale—Short Form [23]. This 14-item tool was developed originally in Canada and has been translated into Kiswahili and determined to be valid and reliable [24]. Higher scores indicate higher breastfeeding self-efficacy.Postpartum depression: Depression will be measured using the Edinburgh Postnatal Depression Scale (EPDS) [25]. The EPDS is a self-report screening scale with 10 items that can indicate if a respondent has symptoms related to perinatal depression [25,26]. The EPDS is valid for assessing depressive symptoms across the perinatal period with a score >12 considered as high symptoms of depression. The EPDS has been used in a variety of African countries to measure perinatal depression [27-29]. The EPDS has already been translated into Kiswahili and has been modified for contextual differences [30].Postpartum anxiety: Anxiety will be measured using the Generalized Anxiety Disorder (GAD)-7 [31], which is a 7-item scale used to assess GAD. The scale ranges between 0 and 21, with scores of 10 or greater indicative of generalized anxiety at a moderate or severe level. The GAD-7 has already been translated into Kiswahili [32] and has been widely used to measure perinatal anxiety in African countries, including in Tanzania [33,34].Newborn morbidity and mortality: The 6-week follow-up survey will collect information on morbidity (eg, diarrhea, jaundice, or infection), need for readmission due to illness, and mortality.Postnatal clinic attendance at six weeks: The 6-week follow-up survey will collect information on the number and date of postnatal contacts.

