### Statistical Analysis

Data will be analyzed on an intention-to-treat (ITT) analysis basis as well as per protocol analysis (excluding women who requested to stop the program or were lost to follow-up). Data will be analyzed using SPSS (version 29, IBM SPSS Statistics, IBM Corporation). Demographic characteristics will be expressed in means, SDs, and percentages, as applicable, based on group allocation. Any significant differences in baseline characteristics, examined through a chi-square analysis or Mann-Whitney test, will be adjusted for in the analyses. A *P* value of .05 will be considered significant for all outcomes. For all analyses, unadjusted and adjusted models will be reported.

For the effectiveness outcomes, total and summative scores will be reported using means, SDs, and percentages, as appropriate. Analysis of covariance will be used to measure whether scores differ between the two groups, adjusted for the pretest scores and any significant baseline characteristics. For newborn care knowledge, newborn morbidity, newborn mortality, and attendance at postnatal care six-week contact, binary variables will be created, and data will be analyzed using logistic regression.

For the implementation outcomes, descriptive statistics will be used to describe mothers’ experience with ECEM-TZ and outcomes will be reported using means, SDs, and percentages, as applicable. Open-ended questions will be analyzed using thematic analysis [35]. Responses will be transcribed verbatim and translated into English for analysis.

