**Figure 1 figure1:**
[figure not shown]
CONSORT flow diagram. CONSORT: Consolidated Standards of Reporting Trials. As data analysis has not yet been completed, the final numbers for analysis has not yet been confirmed. The completed CONSORT will be available once the results are published.

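### The researchers know allocation, and some result-relevant definitions are open in the article; locking these on an arm-masked file would be a cheap safeguard

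*Protocol article*

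**What the plan says.** - **Who knows the arm.** Randomization, Allocation, and Blinding: "The researchers will be aware of participant allocation but will not be involved in data collection from participants or the randomization process". The same section says of the assessors: "The research assistants will be blinded to allocation at baseline (T1) but not at T2". Mothers cannot be blinded, and the article gives a reason for that. It gives none for the researchers.
- **Who holds the data.** Ethical Considerations: "All data will be entered into REDCap by a research assistant in Tanzania with the first author having access to the data".
- **Covariates.** Statistical Analysis: "Any significant differences in baseline characteristics, examined through a chi-square analysis or Mann-Whitney test, will be adjusted for in the analyses". No list of candidate characteristics is given.
- **Binary outcomes.** For knowledge, morbidity, mortality and six-week attendance, the same section says that "binary variables will be created, and data will be analyzed using logistic regression".
- **Rules already fixed.** Effectiveness Outcomes gives the cut-offs for all five knowledge domains, beginning "binary variables will be created to determine whether mothers can identify three or more newborn danger signs, two or more best practice hand washing", and the 0 to 5 score. Sample Size sets the full score as the goal for the binary knowledge outcome. Statistical Analysis names the intention-to-treat and per-protocol analyses and gives the per-protocol exclusions.
- **Timing.** Figure 1 legend: "As data analysis has not yet been completed, the final numbers for analysis has not yet been confirmed".

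**The concern.** Allocation is known to the mothers throughout and to the research assistants at six weeks, so nothing in the outcome assessment is masked. Derivation and analysis are the only stage left where masking could protect the result. The article instead leaves the researchers aware of the arm, and at least one of them can see the data.

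If whoever settles the remaining definitions knows which women received messages, those choices can drift, without intent, toward the hypothesised benefit. A morbidity definition might take in or leave out a borderline condition. An attendance window might be drawn a few days wider. A baseline characteristic might or might not be put forward for testing. Masked derivation does not stop choices being made late, but it does stop them being steered knowingly toward the intervention. At stake is how far a reader can trust the smaller effectiveness outcomes of an otherwise open trial.

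**Working it through.** **1. The plan's own figure.** Inputs from Sample Size: 90% vs 70%, two-sided alpha 0.05, power 80%; 1:1 allocation. With the pooled-variance formula and no continuity correction:

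n per arm = [z(0.975)·√(2·p̄·(1−p̄)) + z(0.80)·√(p1(1−p1) + p2(1−p2))]² / (p1−p2)²

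with p̄ = 0.80:

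- 1.960·√0.32 = 1.109
- 0.842·√0.30 = 0.461
- (1.109 + 0.461)² / 0.04 = 61.6, so 62 per arm and 124 in total

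The stated 124 is reproduced. Power at 62 per arm is 0.803. At the 143 recruited (about 71.5 per arm, assuming no loss) it is 0.856. Recoding the arm label enters none of these terms, so masking changes neither sample size, nor alpha, nor power.

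**2. What is open and what is fixed in the article.**

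| Element | Place | Status |
|---|---|---|
| Five knowledge cut-offs, 0 to 5 score | Effectiveness Outcomes | Fixed |
| Full score as the binary knowledge goal | Sample Size | Fixed |
| Per-protocol exclusions (stop request, loss to follow-up) | Statistical Analysis | Fixed |
| Pretest score as covariate in the analysis of covariance | Statistical Analysis | Fixed |
| Unadjusted and adjusted models both reported | Statistical Analysis | Fixed |
| Which baseline characteristics are tested for imbalance | Statistical Analysis | Open: a rule, but no candidate list |
| Binary morbidity | Effectiveness Outcomes | Open: examples only |
| Six-week attendance | Effectiveness Outcomes; Outcome Measures | Open: number and dates of contacts are collected, no window is stated, and follow-up calls may run to 10 weeks |
| Item scoring of the modified knowledge questionnaire | Effectiveness Outcomes | Open |
| Women lost to follow-up in the intention-to-treat analysis | Statistical Analysis | Open |

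**3. Which open items need the true arm?** None. Morbidity, attendance, item scoring and the handling of losses can be settled without knowing which arm is which. The baseline tests need two groups, but the labels A and B serve as well as the real ones.

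**4. What would reveal the arm?** Three sources exist only or mainly in the intervention arm: the per-participant message-platform output and the programme evaluation survey (Implementation Outcomes), and the stop requests sent as 'acha' (Final Intervention). The per-protocol set depends on stop requests, so it cannot be populated on a masked file. Its rule is already written, so it can be populated after unmasking without discretion.

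**5. Size of the bias.** The document has no input from which to calculate it.

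**The case against.** **The article is a condensation.** The full protocol or an analysis plan, neither shown, may define morbidity, the attendance window, item scoring and the covariates. This stands: their absence here is not in itself a fault. The point rests on what the article does state, namely that the researchers know allocation. If those definitions were dated and locked elsewhere before the data were seen, little of the concern would remain.

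**The covariate rule is mechanical, and data-driven selection is the greater weakness.** This stands in part. A/B labels leave the significance rule in place, and a prespecified list would be the stronger remedy. Without a candidate list, however, someone still decides what is tested.

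**The researchers may need to know the arm.** Someone must run a messaging programme for one group, and the article does not say who. This stands. It cannot be claimed that the researchers have no use for the allocation, only that the open definitions can be settled without it.

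**Masking is neither complete nor free.** The researchers already know allocation and could link records by study number. This stands and limits the gain.

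**Stronger readings that a reader might infer.** One is that all binary variables and analysis sets are still undecided; the table above shows otherwise. Another is to count the knowledge versions, populations and models, and offer the resulting false-positive rate as the size of the problem. That would describe multiplicity. Both models and both populations are planned outputs, and an analyst looking at arms A and B could run the same tests and keep the smallest P value. Masking would not cure that.

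**Conclusion.** The point holds as a minor, remediable risk of bias. The article openly states that the researchers know allocation. It gives one of them access to the data, describes no masking of the analysis, and leaves five result-relevant items open. This contradicts nothing in the document.

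Two assumptions carry the conclusion. The first is that the unmasked researchers, or people working with them, settle the definitions and run the analysis; the article does not say so. The second is that the definitions are not already locked in a document that is not shown.

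The size of any bias cannot be derived from the article, and no figure should be attached to it. Sample size, alpha and power stay as they are. Masking the arm code would also leave the unmasked six-week telephone assessment untouched, which is a separate matter.

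**What to change.** 1. Export the REDCap data with new study IDs and the arm recoded A/B. An existing team member who does not analyse holds the key.
2. On that file, lock the morbidity definition, the attendance window, the item scoring, the handling of losses in the intention-to-treat analysis, the covariate list and the analysis code. Preferably prespecify the covariates rather than choose them by baseline significance tests.
3. Keep the message-platform data, the stop requests and the intervention-only survey in a separate file until then.
4. Unmask, then populate the per-protocol set by its stated rule.
5. The Figure 1 legend says that analysis was not completed, which does not mean that it had not begun. If it has begun, report who knew allocation when each definition was set.

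**Cost:** a recoded export, a key holder from the existing team, and a slight delay in linking the implementation data. The main downside is that masking is only partial, because the researchers already know allocation and could link records.
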